## Outcome assessments and time points

We will use techniques common in long-term cohort studies to ensure minimum loss to follow-up, such as collection of multiple contact addresses and telephone numbers, mobile telephone numbers and email addresses. Trial outcome assessment time points are shown in Table 1.

**Table 1 BMJOPEN2015009898TB1:** Trial outcome variables, analysis metric, aggregation method and time points

			Time point				
Outcome variable	Analysis metric	Aggregation	Baseline	Day 1 postoperative	Day 2 postoperative	Week 6 postoperative	Month 12 postoperative
VAS (0–100 mm)	Final value	Mean		× (before and after physiotherapy)	× (before and after physiotherapy)		
4-point pain scale	Final value	Proportion and type		×	×		
Total use of opiate analgesia (mg)	Final value	Mean		×	×		
Straight leg raise (yes/no)	Final value	Proportion		×	×		
Knee ROM (degrees)	Final value	Mean		×	×		
Timed Up and Go (impaired mobility yes/no)	Final value	Proportion		×	×		
Bed transfers (4-point ordinal scale)	Final value	Proportion and type		×	×		
Distance mobilised (metres)	Final value	Mean		×	×		
OKS	Final value	Mean	×			×	×
EQ-5D-5L	Final value	Mean	×			×	×
DN2 (7-item DN4 ordinal scale)	Final value	Proportion	×			×	×
Adverse events	Final value	Proportion and type		×	×	×	×

DN, Douleur Neuropathic Pain Score; EQ-5D-5L, EuroQol; OKS, Oxford Knee Score; ROM, range of motion; VAS, visual analogue scale.

Our primary outcome measure will use the well-established 100 mm VAS reported by the participant prior to physiotherapy on first day postoperatively, as this is when the patient would be expected to get out of bed and mobilise the knee after their surgery. The mean VAS score will be reported for both treatment groups. A further VAS measurement will be performed before physiotherapy on the second day. This will allow us to define the analgesic effect following mobilisation. Any failure to mobilise and the reason for failure will be recorded from the patient's physiotherapy record. Additional routine standard of care pain score data will be collected during the patient's hospital admission. The pain score is a four-point ordinal scale. The pain data will be reviewed by the research associate and entered onto an anonymised participant data sheet. Early knee function will be assessed by an independent physiotherapist in both groups of patients using four basic methods:
SLR: with patient supine the participant is to attempt (unaided) to flex at the hip with knee locked in extension to raise their operated-side ankle off the bed. If the participant is able to raise ankle at least 5 cm off bed the bed, they are deemed to be able to SLR. The proportion of participants able to SLR in each group will be reported.Knee range of movement: the patient's own active knee range of motion (ROM) to both extension and flexion will be measured in degrees. The mean knee ROM in each group will be reported.The participant is assessed in their ability to transfer from bed to chair: (1) independently, (2) with assistance of one, (3) with assistance of two and (4) unable to mobilise. The proportion of participants in each group will be reported for this ordinal scale.TUG is a test of functional mobility. It uses the time that a person takes to rise from a chair, walk 3 m, turn around, walk back to the chair and sit down. During the test, the patient is expected to wear their regular footwear and use any mobility aids that they would normally require. A time of >20 s indicates impaired mobility. The proportion of participants with impaired mobility in each group will be reported.

At 48 h postoperatively, participant drug charts and anaesthetic charts will be reviewed by the research associate. Opiate analgesia used will be converted to ‘morphine equivalent dose’ (see table 2).^22^ Total morphine equivalent dose used up to 24 and 48 h postoperatively will be recorded for each participant in milligrams and the mean dose reported for each treatment group. The total dose of paracetamol and/or NSAIDS will also be reported.

**Table 2 BMJOPEN2015009898TB2:** Opiate analgesia converted to morphine equivalent dose

Opiate analgesia	Route	Typical dose	Total 24 h dose	Equivalent morphine 24 h dose	Four hourly oral morphine dose	Relative potency to oral morphine (24 h)
Codeine^22^	Oral	60 mg four times a day	240 mg	24 mg	4 mg	0.1
Dihydrocodeine^22^	Oral	60 mg four times a day	240 mg	24 mg	4 mg	0.1
Tramadol^22^	Oral	50 mg four times a day	240 mg	40 mg	6.6 mg	0.2

At 6 weeks and 12 months postoperatively, all participants will asked to complete some questionnaires either at their routine clinical follow-up appointment or via post. The questionnaires will ask participants to complete three validated outcome scores:
OKS will assess participant's perceived function following their procedure. This is a validated self-administered osteoarthritis outcome measure and should only require 10 min to complete.^23^ The mean final value for OKS will be reported for both treatment groups at 6 weeks and 12 months.EQ-5D-5L is a validated measure of health-related quality of life, consisting of a five-dimension health status classification system and a separate VAS.^24^
^25^ The mean final value for EQ-5D-5L will be reported for both treatment groups at 6 weeks and 12 months.DN2/seven-item DN4, a validated screening tool for neuropathic pain consisting of two questions.^16^
^17^ The proportion of participants with evidence of neuropathic pain in each group will be reported.

All AEs will be recorded up to 12 months after surgery*.* An AE is defined as any untoward medical occurrence in a participant and which does not necessarily have a causal relationship with the treatment. A serious adverse event (SAE) is an AE that fulfils one or more of the following criteria:
Results in death;Is immediately life-threatening;Requires hospitalisation or prolongation of existing hospitalisation;Results in persistent or significant disability or incapacity;Is a congenital abnormality or birth defect;Is an important medical condition.

Suspected unexpected serious adverse reactions are SAEs that are unexpected, that is, their nature or severity is not consistent with the summary of product characteristics, and are considered to be caused by one or more of the trial medicinal interventions.

The following (serious) AEs will be expected and therefore will not need immediate reporting to the trial office: chest infection, urinary tract infection, myocardial infarction, stroke, superficial surgical site infection, deep surgical site infection, bleeding, removal/revision of metalwork, deep vein thrombosis (DVT)/Pulmonary Embolism (PE), damage to nerves in the surgical area. The total number, type (with proportions) of AEs will be reported for both groups.

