## Objectives

The primary objective of this full trial is to quantify and draw inferences on the efficacy between treatment groups based on observed differences as shown by a validated, patient-reported 100 mm visual analogue pain score, prephysiotherapy on the first postoperative day, collected by an independent physiotherapist. This is the most important outcome as pain at the time when the patient is first starting to walk and use their new knee replacement will determine the ability of the patient to mobilise. Early mobilisation is associated with improved functional outcomes and a reduced risk of complications.^15^

The secondary objectives of the study are to quantify and draw inferences on the efficacy of the treatment groups based on observed differences as shown by:
Visual analogue scale (VAS) after physiotherapy on the first postoperative day and before and after physiotherapy on the second postoperative day.The total use of opiate analgesia up to 24 and 48 h after the operation.Ordinal pain score (routinely collected up to 40 min after surgery).Independent routine functional physiotherapist assessment on days 1 and 2 postoperatively assessing: straight leg raise (SLR), knee range of movement, Timed Up and Go (TUG), bed transfers and distance mobilised.Oxford Knee Score (OKS) collected preoperatively and 6 weeks postoperatively.EuroQol (EQ-5D-5L) Score collected preoperatively and 6 weeks postoperatively.Douleur Neuropathic Pain Scores (DN2/seven-item DN4) collected preoperatively and 6 weeks and 12 months postoperatively.^16^
^17^The number and type of adverse events (AEs) up to 12 months postoperatively.

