## Methods and analysis

The protocol (V.5.0 dated 7 October 2015) was prepared in accordance with the Standard Protocol Items: Recommendations for Interventional Trials (SPIRIT) guidelines.^18^ This study is jointly sponsored by the University of Warwick and University Hospitals Coventry and Warwickshire NHS Trust. The trial will be carried out in accordance with the Medicines for Human use (Clinical Trials) Regulations 2004 (SI 2004/1031), amended regulations (SI 2006/1928) and the International Conference on Harmonisation Good Clinical Practice (ICH-GCP); all collaborators will be trained in GCP, and in accordance with this protocol. This trial will be reported in line with the Consolidated Standards of Reporting Trials (CONSORT) statement.

A single-centre two-arm parallel group superiority type trial design will be completed. All patients undergoing an elective primary unilateral TKA under the care of an orthopaedic consultant at University Hospitals Coventry and Warwickshire NHS Trust are potentially eligible for entry to the trial. However, patients with any of the following will not be eligible:
Concomitant medical or psychiatric problems which, in the opinion of the investigator, would prevent completion of treatment or follow-up.Preoperative history of neurological abnormality in the ipsilateral leg, for example, history of stoke, neurogenic pain or previous nerve pain.Specific contraindication to the analgesic agents used:
*Morphine*
i. Hypersensitivity reaction.*Ketorolac*
i. Active or previous peptic ulcer;ii. History of upper gastrointestinal bleeding or perforation, related to previous NSAID therapy;iii. Haemorrhagic diatheses, including coagulation disorders;iv. Hypersensitivity to ketorolac, trometamol or other NSAIDs;v. Moderate or severe renal impairment (serum creatinine >160 μmol/L).*Levobupivacaine*
i. Known hypersensitivity to levobupivacaine, local anaesthetics of the amide type or any of the excipients;ii. Uncontrolled angina;iii. Second or third degree heart block.Participation in a clinical trial of an investigational medicinal product (IMP) in the past 90 days.Previous entry in the present trial.Evidence that the patient would be unable to adhere to trial procedures.

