## Statistical analysis plan

Standard statistical summaries (eg, means and variances, medians and ranges or proportions dependent on the distribution of the outcome) and graphical plots showing correlations will be presented for the primary outcome measure and all secondary outcome measures. Baseline data will be summarised to check comparability between treatment arms, and to highlight any characteristic differences between those individuals in the study, those ineligible and those eligible but withholding consent.

The main analysis will investigate differences in the primary outcome measure, the VAS pain score prephysiotherapy on the first day postoperatively, between the two treatment groups (single injection femoral nerve block and multimodal periarticular injection) on an intention-to-treat basis. Initial analysis will investigate differences in pain score measurements on an intention-to-treat basis using a t test based on an assumed normal distribution for the primary outcome (VAS pain score). Tests will be two-sided and considered to provide evidence for a significant difference if p values are less than 0.05 (5% significance level). Estimates of treatment effects will be presented with 95% CIs. The simple t test will be augmented with a linear regression analysis that adjusts for expected confounders of age and gender. Adjusted and unadjusted analyses will be presented together with diagnostics that assess the modelling assumptions (eg, quantile-quantile plots). Subsidiary analyses will also test for differences at intermediate times and more generally across all times using a repeated-measures approach (eg, generalised estimating equations). For secondary outcome measures that can be assumed to be approximately normally distributed (eg, OKS, EQ-5D), data will be analysed in a similar manner to VAS pain scores. However, routinely collected pain scores, measured on a four-point ordinal score scale, will be analysed using the proportional odds model and the time course modelled using appropriate methods (eg, repolr). Counts of AEs will be compared between groups using χ^2^ tests.

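### Preoperative DN2 is collected, but the protocol describes only follow-up proportions by arm; the implied comparison is unbiased, can lose some precision, and does not separate new from persisting positives (minor)

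*Protocol article*

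**What the plan says.** All places are in the protocol article.

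- **Objectives.** DN2 is a secondary outcome: "Douleur Neuropathic Pain Scores (DN2/seven-item DN4) collected preoperatively and 6 weeks and 12 months postoperatively". The secondary outcomes serve to "quantify and draw inferences on the efficacy of the treatment groups based on observed differences as shown by" the listed measures.
- **Outcome assessments and time points, Table 1.** The row that begins "DN2 (7-item DN4 ordinal scale" has marks at baseline, week 6 and month 12. Its analysis metric is the final value and its aggregation is a proportion.
- **Outcome assessments and time points, text on DN2.** "The proportion of participants with evidence of neuropathic pain in each group will be reported".
- **Statistical analysis plan, covariates.** The only covariates named are in "a linear regression analysis that adjusts for expected confounders of age and gender", which is written for the primary VAS. For approximately normal secondary outcomes, with OKS and EQ-5D as examples, "data will be analysed in a similar manner to VAS pain scores".
- **Statistical analysis plan, baseline.** "Baseline data will be summarised to check comparability between treatment arms".
- **Methods and analysis, exclusions.** "Preoperative history of neurological abnormality in the ipsilateral leg, for example, history of stoke, neurogenic pain or previous nerve pain".

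No test or model is named for DN2. The section on trial organisation and oversight mentions a separate statistical analysis plan, which is not at hand.

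**The concern.** The trial pays for a preoperative DN2 result and the article gives it no role in comparing the arms. Two things follow if the analysis is done as described.

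1. **Precision.** A participant's status before surgery may predict status afterwards. Leaving it out makes the interval for the difference between arms wider than it need be.
2. **Interpretation.** The introduction lists nerve damage among the complications of femoral block, and the intervention text warns about infiltration near the common peroneal nerve. The natural question is therefore how much neuropathic pain is new. A follow-up proportion adds new cases to persisting ones. A baseline table by arm gives totals but does not show who changed.

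**Working it through.** **1. The plan's own figure.** The only sample size calculation is for the VAS: n per arm = 2(1.960 + 1.282)² × (30/12)² = 2 × 10.51 × 6.25 = 131.3, so 132 per arm and 264 in total. This agrees with the article. There is no corresponding figure for DN2, so the rates below are all assumptions.

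**2. Bias.** In 20,000 simulated trials per scenario with no treatment effect and 132 per arm, the mean risk difference was between −0.0004 and 0.0000, both without adjustment and with preoperative DN2 in a linear model. The unadjusted comparison is unbiased.

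**3. What drives the gain.** Adjustment multiplies the variance by about 1 − φ², where φ is the correlation between preoperative and follow-up status. Let b be the share positive before surgery, s the share of those still positive at follow-up, and r the new-onset rate averaged over arms. Then m = bs + (1 − b)r and φ = b(s − m) / √[b(1 − b)m(1 − m)].

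With new onset of 3% v 12% (r = 0.075):

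- b = 1%, s = 70%: m = 0.0813, φ = 0.23, variance ratio 1/(1 − φ²) = 1.05 to 1.06
- b = 2%, s = 70%: m = 0.0875, φ = 0.31, ratio 1.11
- b = 5%, s = 70%: m = 0.1063, φ = 0.44, ratio 1.24
- b = 2%, s = 20%: m = 0.0775, φ = 0.07, ratio below 1.01

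Simulation gave ratios of 1.06, 1.11 and 1.25 for the first three, and 1.00–1.02 across persistence of 10–30% with b = 1–2%.

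**4. Power.** Two-sided 5%, 132 per arm, 200,000 trials per scenario, persistence equal in both arms. Unadjusted chi-squared against Mantel-Haenszel stratified by preoperative DN2, 3% v 12% new onset:

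| Positive before surgery | Persistence 50% | 70% | 90% |
|---|---|---|---|
| 1% | 79.1 v 80.9% | 78.5 v 81.3% | 77.2 v 81.7% |
| 2% | 76.2 v 79.0% | 74.2 v 79.3% | 72.1 v 80.6% |
| 5% | 67.3 v 72.6% | 63.1 v 73.9% | 59.1 v 77.6% |

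- Over 3% v 12% and 5% v 15%, with persistence of 50–90%, the gain is 0.9–4.5 points at 1% positive before surgery, 1.8–8.5 at 2%, about 4–18 at 5% and 6–28 at 10%.
- With persistence of 10–30% and 1–2% positive, it is about zero to 1.2 points. Examples: 80.9 v 81.5% (3% v 12%, 1% positive, 20% persistence) and 77.8 v 77.6% (5% v 15%, 2% positive, 10% persistence).
- With nobody positive before surgery it is zero.
- With 3% v 6%, power is about 20% or less by either method.
- Under a null of 5% v 5%, both tests rejected in 4.6–5.2% of trials.

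**5. Interval width.** Mean 95% CI width of the risk difference (3% v 12%, 70% persistence), unadjusted v adjusted: 12.9 v 12.5 points at 1%, 13.4 v 12.7 at 2%, 14.6 v 13.1 at 5%.

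**6. New against persisting.** The share of follow-up positives who were already positive is bs / [bs + (1 − b) × new-onset rate]. At b = 1%, s = 70%: 0.007/0.0367 = 19% in the 3% arm and 0.007/0.1258 = 6% in the 12% arm. At b = 2%: 0.014/0.0434 = 32% and 0.014/0.1316 = 11%.

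**7. Choice of estimator.** A Mantel-Haenszel stratum has weight n₁n₀/(n₁ + n₀), which is zero if either arm is empty. With q = (1 − b)¹³², all preoperative positives fall in one arm with probability 2q(1 − q). At 1%, q = 0.265 and the probability is 39%; at 2%, q = 0.069 and it is 13%. A linear model containing only arm and a preoperative DN2 indicator uses the same stratum weights for its arm coefficient, so it has the same limitation.

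**The case against.** The strongest case against is that nothing is fixed. No DN2 test is named. A final-value metric is compatible with a baseline covariate. The main quoted sentence describes reporting, not a comparison. The age and gender text governs the VAS, which has no baseline value, and extends only to roughly normal outcomes, so it does not govern a proportion. A separate analysis plan may settle the model. All of this stands, and it limits the claim to what the text implies. It does not remove the point: the article gives DN2 a metric and an aggregation, and no role for its preoperative value.

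The gain also rests on assumed persistence. Nothing in the documents supports 50–90% over 10–30% for patients whose painful joint is replaced, and the exclusion of known nerve pain in the operated leg points to few preoperative positives. That stands too. The exclusion acts on history, though, not on the DN2 result, so screen-positive patients can still enter.

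A reader might infer that the protocol commits to an unadjusted test, that the comparison is biased, or that a real difference would be missed. The documents support none of these: no test is stated, randomisation protects the unadjusted comparison, and no DN2 rates are given from which a missed effect could be shown.

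**Conclusion.** The point holds as a minor one about efficiency and interpretation. The article collects preoperative DN2 and describes only follow-up proportions, so an unadjusted comparison is implied. That comparison is valid. Adjustment would be worth roughly 0 to 1 point of power if 1–2% are positive before surgery and few persist, about 1 to 8 points if half or more persist, and more if 5% or more start positive. These figures assume 132 per arm, the new-onset rates shown and equal persistence in both arms. With about 5% loss (125 per arm; 3% v 12%, 70% persistence), power is 75.6 v 79.1% at 1% positive and 71.6 v 77.2% at 2%, a similar gain. The power figures come from Mantel-Haenszel and indicate what adjustment can give; they are not results for the estimator proposed below. Separating new from persisting positives is useful whenever anyone is positive before surgery, whatever the power gain.

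**What to change.** In the DN2 text and the statistical analysis section, state that DN2 status at 6 weeks and at 12 months will be compared between arms in all participants with a follow-up result, adjusted for preoperative DN2 status, and reported as a risk difference with 95% CI.

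- **Estimator.** Use a regression-standardised risk difference: fit a logistic model with arm and preoperative DN2, then average the predicted risks under each arm over everyone. A missing preoperative result is kept as its own category, so nobody is dropped. Take the inference from the risk difference and its interval. The logistic likelihood-ratio test rejected in 5.4–5.9% of null trials with 1–5% positive before surgery.
- **Alternatives.** A linear probability model with robust standard errors is simpler and keeps every record in the fit. Like plain Mantel-Haenszel, though, its arm coefficient takes no information from preoperative positives who all fall in one arm, so it is second choice.
- **Reporting.** Keep the raw proportions and add a descriptive table of new and persisting positives by arm.

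The cost is a wording change and a few lines of code, with no new data, visits or participants. The downside is little or no gain in precision if preoperative positives are rare or seldom persist.

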The use of opioid drugs, administered by means of either patient-controlled analgesia or other methods, is another effective method of postoperative pain relief but is often associated with systemic side effects, including nausea and vomiting, respiratory depression, drowsiness, pruritus, reduced gut mobility, and urinary retention.^6^ Drowsiness in particular may delay the patient's postoperative mobilisation. Femoral nerve block, as a single perioperative infiltration or via an indwelling catheter, has been shown to improve postoperative pain control and reduce the use of systemic analgesics and is currently the standard care for perioperative analgesia.^7^ The key advantage of the technique is that it avoids the systemic effects associated with both epidural and opioid analgesics. However, it may be associated with complications such as vascular puncture, nerve damage, infection and diminished muscle control.^8^ The inhibition of the quadriceps muscle group can delay postoperative mobilisation.^9^ Since the posterior capsule of the knee joint is innervated by the branches of the sciatic nerve rather than the femoral, femoral nerve blockade may also result in incomplete pain relief. Femoral nerve block is currently the standard perioperative analgesia for TKR surgery among anaesthetists working within the NHS.

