## Ethics and dissemination

The definitions of the EU Directive 2001/20/EC article 2 based on ICH-GCP apply in this trial protocol. Both investigators and sponsors will follow specific procedures when notifying and reporting AEs/adverse reactions in this trial. SAEs that are not listed as expected will be considered to be related or potentially related to the administration of the IMP. Expectedness will be determined by the investigators using the information within the products SPC. SAEs that are deemed to be unexpected and related to the trial will be notified to the main research ethics committee, MHRA and trial sponsor within 15 days for a non-fatal or non-life-threatening event and within 7 days for a fatal or life-threatening event. All participants experiencing SAEs will be followed-up as per protocol at the end of the trial and causality of SAEs assessed.

Participant in the study are covered by indemnity for negligent harm through the standard NHS indemnity arrangements. The University of Warwick has insurance to cover for non-negligent harm associated with the protocol. The liability of the manufacturer of medicinal products being administered is strictly limited to those claims arising from faulty manufacturing of the product.

The results of the trial will be disseminated via patient information material prepared in collaboration with NHS Choices. All key findings from the trial will be presented at national and international conferences such as the British Orthopaedic Association (BOA) and British Association of Specialist Knee Surgeons (BASK), and we aim to publish the results in at least one major peer-reviewed publication.

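### Expectedness of serious adverse events is set by two conflicting rules, so a listed event suspected to be drug-caused can miss or be late for expedited notification

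*Protocol article*

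**What the plan says.** Three statements in the protocol article bear on whether an SAE counts as expected.

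- **Fixed list** (Outcome assessments and time points): certain adverse events, serious ones included, "will be expected and therefore will not need immediate reporting to the trial office". Ten types follow: chest infection, urinary tract infection, "myocardial infarction, stroke, superficial surgical site infection, deep surgical site infection, bleeding", removal or revision of metalwork, DVT/PE, and "damage to nerves in the surgical area". The exemption carries no condition on cause or severity.
- **SUSAR definition** (same section, just before the list): an SAE is unexpected when "their nature or severity is not consistent with the summary of product characteristics". It must also be considered caused by a trial medicinal intervention.
- **SPC rule** (Ethics and dissemination): "Expectedness will be determined by the investigators using the information within the products SPC". SAEs that are both unexpected and related go to the ethics committee, the MHRA and the sponsor within 7 days if fatal or life-threatening, and within 15 days otherwise.

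The list has a second use under Ethics and dissemination: "SAEs that are not listed as expected will be considered to be related or potentially related to the administration of the IMP". No matching statement is made about listed SAEs. The same section says that causality of SAEs is assessed, in a sentence that also speaks of follow-up at the end of the trial.

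**The concern.** Expected has two meanings here: on the list, or consistent with the SPC. The list does not present itself as drawn from the SPCs. Some entries, such as revision of metalwork, are on their face complications of the operation. It also ignores severity, which the SUSAR definition makes part of the test.

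At stake is the prompt handling of individual serious events in a trial of medicinal products. Site staff who follow the list would have no duty to tell the trial office at once about, say, a serious bleed, even if they suspected a trial drug. The article itself ties some listed events to the interventions, so the overlap is not merely theoretical.

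**Working it through.** There is nothing to compute: no sample size, power or event figure enters. The check is to apply each rule to each kind of SAE and see where the answers differ.

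| SAE | SPC rule and SUSAR definition | Fixed list | Conflict? |
|---|---|---|---|
| Listed, suspected drug-caused, not consistent with SPC | Unexpected and related: SUSAR, 7 or 15 days | Expected, no immediate report | **Yes** |
| Listed, suspected drug-caused, consistent with SPC | Expected: no expedited notification | Expected, no immediate report | No |
| Listed, not drug-caused | Not a SUSAR | Expected, no immediate report | No |
| Not listed | Judged by SPC; treated as related or potentially related | Exemption does not apply | No |

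The conflict is confined to the first row, but there the answers are opposite.

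**Can that row be occupied?** Two places in the article suggest so.

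1. *Bleeding.* The eligibility criteria (Methods and analysis) exclude, under ketorolac, patients with haemorrhagic diatheses or previous NSAID-related upper gastrointestinal bleeding. Of the two allocated interventions, only the periarticular injection contains ketorolac (Interventions). Bleeding is on the list without qualification.
2. *Nerve damage.* The Interventions section asks for care to avoid excessive infiltration near the common peroneal nerve. That nerve is at the knee, so an injury there would fall within the listed wording.

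These links show that a listed event may be suspected to come from a trial drug or its delivery. They do not show that it would be inconsistent with the SPC, because the SPCs are not in the document.

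**How a delay would arise.** A listed event need not reach the trial office at once. If notification depends on the trial office knowing of the event (an assumption, since the article does not set out the workflow), a first-row event can pass its 7- or 15-day limit before anyone there judges it. Early causality assessment could catch it, but the one sentence on causality leaves the timing unclear.

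**The case against.** The strongest reply is that the article condenses a full protocol (V.5.0) and refers to specific procedures for notifying adverse events and reactions. Exceptions for drug-caused events may be written there. That would excuse missing detail. It does not excuse two stated rules that give opposite answers, and the list is worded as a general exemption.

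A second reply is that the SPC rule, supported by the SUSAR definition, plainly governs regulatory notification, so a first-row event still starts the clock. This stands in part: the clock is not abolished. But the list then removes the prompt report on which meeting the clock is likely to depend.

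Several stronger readings are tempting, and the text does not support them.

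- *That such events go unreported, or that oversight is blind to an arm difference until the final analysis.* All adverse events are recorded to 12 months and reported for both groups, and counts are compared by chi-squared tests (Statistical analysis plan). The DMC reviews interim data and safety (Trial organisation, regulation and oversight), and nothing removes listed events from that review. These safeguards do not replace prompt notification of single cases, but they rule out non-reporting as the consequence.
- *That listed events are presumed unrelated.* Treating unlisted SAEs as potentially related does not imply the converse, and the text says that SAE causality is assessed.
- *That the Introduction's account of femoral block, with "complications such as vascular puncture, nerve damage, infection and diminished muscle control", shows exempted harms.* The block is placed just below the inguinal ligament, while the list covers nerves in the surgical area and surgical site infections. Harm at the block site may lie outside the list. The peroneal nerve caution and the ketorolac exclusions are better evidence.

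**Conclusion.** The contradiction is real and narrow. For a listed SAE that is suspected to be caused by a trial drug and is not consistent with the SPC in nature or severity, one rule requires notification within 7 or 15 days, while the other removes the duty of immediate reporting to the trial office. Expedited notification can therefore be delayed or missed.

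The size cannot be given as a number. Ten event types carry the exemption. The article links at least two of them, bleeding and nerve damage in the surgical area, to a trial drug or its delivery. Which types would be unexpected against the SPCs cannot be settled from this document, and event numbers cannot be estimated from it. A reader might infer that the clocks can never start for any listed event; that goes too far, since the SPC rule is also in force.

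The primary comparison, the type I error rate and the power are unaffected. The conclusion rests on the article's wording and on the assumption that timely notification depends on the trial office hearing of the event promptly.

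**What to change.** Reconcile the adverse-event text in Outcome assessments and time points with Ethics and dissemination:

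1. State that the SPC governs expectedness for any SAE suspected to be related to a trial drug, whether or not it is listed.
2. Limit the list's exemption from immediate reporting to events judged unrelated to the trial interventions.
3. State that causality of every SAE, listed ones included, is assessed when the event occurs rather than at the end of the trial.

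Keep the default that unlisted SAEs are treated as potentially related. It errs towards reporting, and removing it would weaken the safeguards.

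The cost is a short protocol amendment and slightly more immediate SAE reports. If the full protocol already contains these conditions, aligning the wording is enough.
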